## 4.0 STUDY DESIGN

The study, to be conducted in two phases, will examine procedural and clinical outcomes, as well as participant and provider acceptability, of adaptations of the Shang Ring technique for male circumcision that would simplify its use and increase its acceptability.

- Phase I will be non-comparative for exploration of the no-flip technique for Shang Ring circumcision (i.e. all participants will be circumcised using the no-flip Shang Ring technique). Historical data from standard Shang Ring circumcisions conducted in Africa (Kenya, Uganda and Zambia) will be used as the comparison group. Men will be randomized to removal at 7 days after circumcision vs. delayed removal, to assess occurrence and safety of spontaneous detachments following circumcision with the no-flip technique.
- Phase II will compare the use of topical vs. injectable anesthesia for Shang Ring circumcision. Participants will be randomized to topical vs. injectable anesthesia in a 2:1 ratio. We rationalize the 2:1 randomization scheme given that we will have just completed Phase I in which 200 men and boys will have been circumcised using the no-flip technique with injected anesthesia. However, given the subjectivity associated with using reported pain as the primary endpoint, we believe it is critical to randomize participants in this phase of the study.

Because of the possibility that boys and men could have different outcomes after no-flip Shang Ring circumcision or could respond differently to use of topical anesthesia, we

will recruit participants equally in two age groups in both phases; 50% of participants recruited in each phase will be between 10-15 years old and the other 50% over 15 years old. Because recruitment shall be taking place at two sites, which may have different recruitment rates, and because clients need to be randomized 1:1 and 2:1 into the Phase 1 and Phase 2 treatment groups, respectively, appropriate stratified block randomization techniques by age will be applied to achieve the intended number of participants per treatment group.

We expect the Shang Ring to receive WHO prequalification while the study is ongoing, and once this happens, there will be an interest in moving the Shang Ring into programmatic use as quickly as possible. Knowing the safety of the no-flip approach and whether or not topical anesthesia is feasible sooner rather than later may facilitate introduction of the device. Given this, we may overlap the two phases of the study if that seems logistically feasible based on study performance. For example, if it is clear that the no-flip technique is safe and acceptable at that time that recruitment is completed in the Phase I, we may begin recruitment into Phase II while follow-up is being completed in Phase I. Alternatively, because the age groups are the same in the two phases, i.e. 10-15 years old and over 15 years old, we could start Phase II in one age group as soon as recruitment into Phase I in that age group has been completed, assuming that we have sufficient evidence regarding the safety and acceptability of the no-flip technique. For example, after 115 boys less than 15 years old have been enrolled in Phase 1, we could start enrollment for Phase II in that age group. This decision will be made in consultation with the Data Safety and Monitoring Board (see section 9.3)

Below is a diagrammatic representation of the two phases of the study, which outlines the visits and procedures to be carried out during each visit.

## Phase I

[figure not shown]

## Phase II

[figure not shown]

## 5.0 STUDY SITES

This study will be conducted at two primary sites in Kenya: (1) Homa Bay County Hospital, Homa Bay County, in the western region, and (2) Vipingo Health Center, in Kilifi County, along the coast. The study sites were determined in conjunction with NASCOP VMMC National coordinator and county health authorities. Circumcisions will be done by trained medical officers, clinical officers or nurses.

Staff at the Homa Bay County Hospital have had extensive experience with use of the Shang Ring in adults, having been the site where the previous four Shang Ring studies with adults described earlier were conducted. They also have experience with Shang Ring circumcisions in boys under 18 years old as the county hospital was the site for the Shang Ring in children pilot study described above.

Staff from the site in Vipingo conduct conventional surgical circumcisions in men and boys but do not currently have experience with the Shang Ring. Clinical officers and nurses from the site will be trained on the Shang Ring procedures by staff from Homa Bay prior to study enrollment. The staff from Homa Bay have experience training other male circumcision providers on use of the Shang Ring, having previously trained providers from other facilities in Kenya, as well as from Uganda and Zambia.

Due to the volume of men that we plan to recruit in a relatively short time period, each primary site may use outreach services or additional clinics to recruit and circumcise study participants similar to what we did in the Shang Ring Demonstration Study conducted in 2012 in Homa Bay (KEMRI NON-SSC protocol # 299) where we involved five satellite sites and incorporated outreach activities within Homa Bay district.

The priority sub-counties for additional recruitment within Homa Bay County will be selected with guidance from County Health Management Team. This will similarly be how priority sub-counties would be selected around our Vipingo site. Previously, within Homa Bay county, Ndiru and Nyangoro Health Centres participated in the Demonstration Study and still have staff that were previously trained on Shang Ring VMMC technique.

## 6.0 STUDY PARTICIPANTS

### 6.1 Population Base

Participants will be recruited for the study from boys and men, 10 years and older who are seeking MC at one of the study sites. A total of 575 participants shall be enrolled into the study (230 in Phase I and 345 in Phase II). Because of the possibility that boys and men could 1) have different outcomes following no-flip Shang Ring circumcision or 2) respond differently to use of topical anesthesia, we will recruit participants in two age groups, with half of the participants in each phase being 10-15 years old and the other half being over 15 years of age.

### 6.2 Inclusion Criteria

All participants enrolled in this research study must meet the following inclusion criteria:

- Aged 10 years and older;
- Uncircumcised upon clinical examination;
- In good general health;
- Free of genital ulcerations or other visible signs of STI upon clinical examination;
- Participant and parent or legally acceptable representative (LAR) as applicable must be able to understand study procedures and requirements of study participation;
- Freely consents to participate in the study and signs a written informed consent form if 18 years of age or greater
- Accompanied by the parent/LAR, who freely consents and signs an informed consent form for participation of the child into the study for participants less than 18 years old;
- Assent from participant less than 18 years old who understand study procedure;
- Participant must agree to return to the study site for the full schedule of follow-up visits after his circumcision (or as appropriate the Parent or LAR must agree to bring the participant);
- Participant and parent/LAR as appropriate must agree to provide the study staff with an address, phone number, or other locator information while participating in the research study.

VCT will be offered according to the Kenya National VMMC guidelines to potential participants. Participants who undergo VCT (or the parents/LAR of those participants) may or may not make known their results to the study staff.

### **6.3 Exclusion Criteria**

A client will be excluded from participation in this research study if he has any of the following exclusion criteria:

- Has a known allergy or sensitivity to lidocaine or other local anesthesia;
- Takes a medication that would be a contraindication for elective surgery, such as an anticoagulant or steroid;
- Has known bleeding/clotting disorder (e.g. hemophilia);
- Has any congenital genitourinary abnormality;
- Has an active genital infection, anatomic abnormality or other condition (e.g. diabetes or sickle cell anemia), which in the opinion of the surgeon, prevents the man from undergoing a circumcision as part of this study; or,
- Is currently participating in another biomedical research study.

### **6.4 Client Withdrawal/Discontinuation**

Participants may withdraw from the study at any time without loss of services to which they may normally be entitled to at the site. Study staff members will record reasons for discontinuation. Every reasonable effort will be made to assess information relevant to study outcomes at the time of discontinuation and refer the participant for follow-up care as needed.

Once a subject has undergone a circumcision procedure, he will continue in the study for all scheduled visits, even if study recruitment is halted.

If withdrawal of a client happens reasonably before the anticipated end of the study period as a whole, recruitment efforts shall be made to replace the participant in the particular study group he belonged.

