### **Phase I**

In Phase I, the Shang Ring circumcision will be completed using the no-flip technique described above for all enrolled participants. Participants will be randomized 1:1 prior to the start of the circumcision procedure to removal at 7 days or spontaneous detachment. Local anesthesia will be induced via dorsal penile nerve block (DPNB) using 1% lidocaine without epinephrine, as per WHO recommendations (WHO 2008) and Kenya national VMMC practice. This is what has been used for local anesthesia in our previous Shang Ring studies in Africa. Because of the possibility that boys and men could have different outcomes, we will recruit participants equally in two age groups; 50% ages 10-15 years old and 50% over 15 years old.

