### **Phase II**

Assuming positive outcomes of Phase I, we will use the no-flip technique for all Shang Ring circumcisions in Phase II.iv In this phase, participants will be randomized to topical or injectable anesthesia in a 2:1 ratio. We rationalize the 2:1 randomization scheme given that we will have just completed Phase I in which 230 men and boys will have been circumcised using the no-flip technique with injected anesthesia. However, given the subjectivity associated with using reported pain as the primary endpoint, we believe it is critical to randomize participants in this phase of the study. Because of the possibility that boys and men could respond differently to use of topical anesthesia we will recruit participants equally in two age groups; 50% ages 10-15 years old and 50% those over 15 years old.

To get a better sense of minimum dwell time necessary for adequate anesthesia, we will test for anesthetic effect more frequently (e.g. every 3-5 minutes) in the first 10 participants randomized to the topical arm in each age group (10-15 and over 15 years old), as well as any participants randomized to the injectable arm during this period. During this time we will also closely monitor the occurrence of any significant problems with application of the topical anesthesia or potency of the anesthesia with the topical agent. This will allow us to establish a minimum dwell time which will be important for logistic and program planning purposes, although each participant will be tested for numbness as described below before the circumcision procedure is started. Given the previous experience with use of EMLA cream for male circumcision, we are expecting that it will provide adequate anesthesia for Shang Ring circumcision. Should we determine that in fact it does not, or that there are unexpected problems, we may explore other options such as 4% or 5% lidocaine cream.

---

iv Given the experience with the no-flip technique in China and our experience with the technique in the pilot study on use of the Shang Ring in children in Kenya, we are not expecting any outcomes that might suggest that the no-flip technique is inappropriate, however, should that be the case, we will use the standard Shang Ring technique for circumcisions in Phase II.

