## 9.0 STATISTICAL CONSIDERATIONS

### 9.1 Study Size Justification

By recruiting 230 participants into Phase I of the study we expect to have complete follow-up data on at least 200. This sample size number is in line with the recommendations from the World Health Organization for clinical evaluation of MC devices, which is based on an ability to rule out an AE rate of about 5% with a new use of a device that has already been shown to be safe in a larger group of men in RCTs and demonstration studies. (WHO 2012)

In Phase II, by recruiting 345 participants, we expect to have complete follow-up data on at least 300. For comparing postoperative pain scores, we will randomize 345 males in 2:1 ratio to topical vs. injectable anesthesia for circumcision. This sample would provide 100% power to detect a mean difference of 1 on the 0 to 10 pain scale using a 2-sided test at the 0.05 significance level. This calculation assumes a standard deviation of 1.8, which is based on prior data. For other binary endpoints, this sample size will provide at least 80% power to detect absolute differences in proportions between groups of at least 20% separately within each site using two-sided tests at the 0.05 significance level. We will not make any adjustments for multiple comparisons between randomized groups.

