- For Phase II, the interim analysis will be conducted after 40 men have been circumcised in each age group in the topical arm (10-15 and over 15 year olds). At the time of the interim analyses, data on reported pain experienced during the circumcision, safety, study quality, and possibly acceptability will be provided to the DSMB by unmasked treatment group. Although this phase is necessarily open-label, the Lead Study Biostatistician will remain blinded to treatment group until the final analyses have been verified. An independent biostatistician, not otherwise involved with Phase II of the study, will prepare the unmasked tables for the DSMB.

The following stopping guidelines are proposed for the DSMB regarding reported pain experienced during the procedure and adverse events in the second phase of the study:

1. At the time of the interim analysis, the DSMB may recommend stopping the study or temporarily halting recruitment if there are notably more severe adverse events among cases using topical anesthesia compared to those using injectable anesthesia (the DSMB will decide the level of significance they will use).
2. In the event that the interim analysis shows notably fewer moderate and severe adverse events among topical anesthesia cases compared to participants receiving standard injectable anesthesia, the study should continue in order to gather additional data on outcomes following use of topical anesthesia with the Shang Ring, such as time to healing and potential rare adverse events.

If the study is stopped temporarily or permanently for any reason, follow-up of participants already enrolled will continue for all the planned follow-up visits; longer if necessary to document complete healing. Enrolled participants will receive continued clinical care as necessary.

It should be noted that if there appears to be an unexpectedly high number of serious adverse events in either phase of the study, any one of the study IRBs may temporarily or permanently halt the study at any time. In addition to IRB oversight, the study clinicians, site PIs and the PEC will review all SAE's as well as severe, related adverse events and closely track other AEs throughout the study.

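### Section 6.4 replaces a withdrawn participant within his own undefined study group, and nothing says the replacement is randomised

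*Combined protocol and SAP*

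**What the plan says.** Section 6.4 sets a condition, "If withdrawal of a client happens reasonably before the anticipated end of the study period as a whole", and then the rule: "recruitment efforts shall be made to replace the participant in the particular study group he belonged". It does not define study group, say how the replacement is allocated, separate withdrawals before circumcision from those after it, or say whether replacements count within the planned totals.

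Both phases contain a randomised allocation:
- Phase I (section 8.2): "Participants will be randomized 1:1 prior to the start of the circumcision procedure to removal at 7 days or spontaneous detachment".
- Phase II (section 8.2): "participants will be randomized to topical or injectable anesthesia in a 2:1 ratio".
- Method (section 4.0): "appropriate stratified block randomization techniques by age will be applied to achieve the intended number of participants per treatment group".

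None of these passages makes an exception for replacements. Section 9.3 says of Phase II: "Although this phase is necessarily open-label". For Phase I's main question, section 4.0 says: "Phase I will be non-comparative for exploration of the no-flip technique for Shang Ring circumcision". The allowance for incomplete follow-up is in section 9.1: "By recruiting 230 participants into Phase I of the study we expect to have complete follow-up data on at least 200", with 345 recruited for at least 300 in Phase II.

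**The concern.** If study group means arm, a vacancy in the injectable arm is filled by recruiting someone for the injectable arm. That person is not randomised, and staff seeking him know which arm they are filling. Random allocation and concealment are both lost for him.

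The plan gives reasons to care. Sections 4.0 and 8.2 treat randomisation as essential in Phase II because the primary endpoint is subjective reported pain. Section 1.2 calls injection the most painful step and notes that fear of needles may keep some men away. A needle-averse man allocated to injection might therefore leave before the procedure. A replacement recruited for that arm would be someone willing to be injected, a trait that could well relate to reported pain. This is an illustration, not something the documents report.

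In Phase I the stake is smaller. The randomised contrast, removal at day 7 against spontaneous detachment, serves a secondary objective.

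**Working it through.** **1. What study group most naturally means.** For age strata the plan consistently writes *age group* (Summary; sections 4.0, 6.1, 8.1, 8.2). For arms it writes *treatment group* (4.0), *spontaneous detachment group* (7.2, 8.3), *7 day removal group* (8.3), *topical group* (8.2) and *randomization group* (9.2). The arm is the likelier meaning, but the term in 6.4 matches none of these exactly.

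**2. The plan's own power figure.** Inputs from section 9.1: difference 1 on the 0 to 10 scale, SD 1.8, two-sided 0.05, 345 randomised 2:1 (230 topical, 115 injectable). Normal approximation:

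power = Φ(δ / [σ√(1/n₁ + 1/n₂)] − 1.96)

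- 115 and 230: standard error 1.8 × √(1/115 + 1/230) = 0.2056; 1/0.2056 = 4.864; Φ(2.904) = 0.998. The noncentral t gives the same, so the stated 100% is reproduced as a rounding.

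**3. Power without any replacement.**
- 300 evaluable (100 and 200): standard error 1.8 × √(1/100 + 1/200) = 0.2205; 1/0.2205 = 4.536; Φ(2.576) = 0.995.
- 20% loss, an assumption, giving 276 evaluable (92 and 184): standard error 0.2298; 1/0.2298 = 4.351; Φ(2.391) = 0.992.

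**4. Losses already covered.**
- Phase I: 230 − 200 = 30; 30/230 = 13.0%.
- Phase II: 345 − 300 = 45; 45/345 = 13.0%.

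**5. Why 13% is only a ceiling on replacements.** It is an allowance for all incomplete follow-up. Section 6.4 replaces withdrawals only, and only sufficiently early ones. Section 10.1 classifies nobody as lost until the site closes, so such losses would not trigger replacement.

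**6. When the Phase II primary endpoint is exposed.** Section 3.2.1 records maximum pain immediately after the procedure, and section 8.2 expects most circumcisions on the enrolment day. A man who withdraws later already has his score. The gap that replacement would fill for this endpoint is therefore mainly withdrawal between randomisation and procedure. Section 6.4 does not exclude replacing a later withdrawal. Doing so would add a non-randomised score, but the randomised score would already exist.

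**7. Illustrative shift in one arm's mean.** Shift = f × d, where f is the fraction of the arm made up of non-randomised replacements and d is how far their mean pain differs from that of randomised participants. Neither is in the documents. Assume f from 2% to 13% (the top value applying the ceiling evenly across arms) and d from 0.5 to 1.8 points (1.8 is one SD):
- Smallest: 0.02 × 0.5 = 0.01 points.
- Middle: 0.05 × 1 = 0.05 points.
- Largest: 0.13 × 1.8 = 0.23 points.

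The target difference is 1 point. Similar replacement in both arms would partly cancel.

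**The case against.** The strongest reply is that nothing in the protocol says replacements bypass randomisation. The plan recruits by phase and age group and then randomises. Replacing a man through recruitment efforts could simply mean finding another client in the same phase and age stratum, who is then randomised like everyone else. That reading is possible, and it means arm-directed assignment is an inference. It does not rescue the sentence: the term is undefined, the arm is its likelier meaning, and the rule as written permits filling a named arm.

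Several stronger readings are tempting but not supported:
- *That informative withdrawals are removed from the analysis.* Nothing says that withdrawn participants leave it. Section 6.4 has staff record reasons and try to collect outcome information at discontinuation. Section 9.2's rule that missing data are ignored is a separate matter.
- *That nobody is blinded.* Section 9.3 keeps the lead biostatistician blinded in Phase II until the final analyses are verified. Only Phase II is called open-label. For Phase I this is inferred from the design, since removing the ring or leaving it on cannot be masked from participant or provider.
- *That both phases are equally affected.* Phase I's primary endpoint is a single-arm adverse event rate, and section 9.2 plans no between-arm test there.
- *That 30 and 45 men would be replaced.* Step 5 of the working shows why those are not replacement counts.

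**Conclusion.** The concern holds as a defect in a stated rule. Section 6.4 permits, and on its most natural reading directs, filling a vacated arm outside the 1:1 and 2:1 age-stratified randomisation. It does not prove that this would happen.

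The likely bias is small. The range of 0.01 to 0.23 points against a target of 1 rests wholly on assumed fractions and differences, so it illustrates scale and is not an estimate. The main exposure is the Phase II pain comparison, through withdrawals between randomisation and procedure. The Phase I removal-timing comparison is secondary.

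What settles the matter is that replacement brings almost nothing: with 300 evaluable, Phase II power is about 99.5% under the plan's own difference and SD. This is a cheap improvement, not a threat to the trial's main conclusions.

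**What to change.** Amend the replacement sentence in section 6.4 in one of two ways:
- randomised participants are not replaced; or
- any additional participant takes the next unused allocation on the age-stratified randomisation list, whatever arm it gives.

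Add that a withdrawn participant's data up to withdrawal are kept and that he is reported under his assigned arm. If the second option is chosen, say whether additional participants count within the 230 and 345.

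This reporting rule does not require changing the as-treated primary analysis in section 9.2, which is a separate question. Section 9.2 already promises to show where as-treated and intention-to-treat differ.

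The cost is a short wording change and slightly uneven final arm sizes. No extra participants are needed, because section 9.1 already covers the expected losses.
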